## Methods

The protocol for this proposal has IRB approval both **from UNM Health Sciences Center IRB # 10249 and Indian Health Services IRB # N10-AQ-10**. Both IHS and the tribal council of Zuni have approved this research. All participants of this pilot education program must be diagnosed with overt diabetes (fasting glucose >126mg/dL, HgA1c>6.5%, or random blood glucose >200mg/dL). The goal is to recruit Zuni adults to attend one group class no larger than 10 individuals. Participants are recruited by native Zuni Community Healthcare Representatives (CHRs) as part of the larger Zuni Health Initiative (ZHI) project. [name] and the ZHI have extensive experience recruiting community members as part of the Zuni Kidney Project (ZKP). The CHRs will contact diabetics identified during the ZKP for recruitment into this study, as well as advertise with fliers around town and in the local newspaper.

As individuals are recruited to the study, baseline measurements taken by the CHR in the home of the participant. Baseline lab work, including a complete lipid panel, CBC, UACR, and serum creatinine collected from each participant at home prior to the class. Clinical measurements such as height, weight, blood pressure and HgA1c is performed on site the day of the class. Point of care (POC) testing is done with HgA1c levels, has the advantage of giving the patient immediate feedback on lab results. A prospective, randomized, controlled study in Australia showed that measuring cholesterol using point of care testing, along with education about lifestyle changes during home visits, led to a statistically significant decrease in cholesterol levels in the interventional group, whereas no change was reported in the control group. In our study, the individual results of the HgA1c is given to each participant at the end of the class, allowing each participant the opportunity to discuss his or her results with the class instructor and to develop personalized strategies for lower HgA1c levels through lifestyle modifications and adherence to a treatment plan.

The Educational Intervention Survey is completed by the participant during the home visit prior to the pilot class. The Educational Intervention Survey is an 8 page survey that included basic demographic information about the participant as well as diabetes specific questions. The diabetes specific questions allow the participants to self-report strategies they use to manage their diabetes and complications they have faced as diabetics.

A Baseline Patient Activation Measure (PAM) score is obtained prior to the pilot class using the 13-item short form PAM questionnaire. The 13 questions use a Likert scale grading with 4 response options: Strongly Disagree (1), Disagree (2), Agree (3), Strongly Agree (4), and N/A. The raw score is then converted to an activation score and the patient is placed in 1 of 4 stages: 1. Believing the patient's role is important but not taking action, 2. Having the confidence and knowledge necessary to take action, 3. Taking action to maintain and improve one's health, 4. Staying the course even under stress. Patients at lower activation levels do not take control of their own health and lack basic knowledge about their condition, whereas patients with high activation scores possess the knowledge, skills, and confidence to self-manage and stay the course under adverse circumstances. Patients with higher activation scores are more likely to exercise on a regular basis, eat a low fat diet with more fruits and vegetables, and abstain smoke, which result in self-reported better health and lower rates of doctor office visits, ER visits, and hospital stays. A retrospective analysis showed that patients with higher PAM scores had better A1C testing results, better A1C control, and lower rates of all-cause hospital discharges. Because higher PAM scores are correlated to better patient outcomes, it is an ideal way to measure if educational classes improve participants' knowledge and perception about diabetes. After our education courses, we hypothesize the participants' PAM scores will increase.

The education class is held at the Zuni Health Initiative building, located across the street from IHS. Each class run for approximately 60 minutes, with 40 minutes of Powerpoint presentations and 20 minutes for questions and interpretation of individual A1C results. Each class consist of 6-10 participants. The classes begin at noon and lunch is provided. The participants are reminded of the class 48-72 hours beforehand, and CHR provide transportation for those who need it.

The educational component of the class follow the nutritional and lifestyle modifications for diabetics recommended by the American Diabetes Association. The class cover the pathophysiology, classification, and the potential complications of diabetes including hypertension, dyslipidemia and kidney disease. The importance of medications and lifestyle modifications, improving diet and exercising 150 minutes per week, for management of diabetes is discussed. We presented portion control as a strategy to improve nutrition by presenting simple ideas participants can use to cut calories. The classes are designed to be interactive, and the participants are encouraged to ask questions during or after the presentation. The classes are also designed to address issues specific to the Zuni culture, including the high rate of kidney disease and type 2 DM in the Zuni population as well as traditional foods and dietary habits that contribute to high caloric intake. Participants are also encouraged to write questions on a note card that are collected at the end of the Powerpoint, so questions can be asked anonymously. Each participant got the opportunity to discuss their A1C value with the instructors after the class.

We believe a Student's t distribution is most closely represent our data. We anticipated that a 2-tailed statistical model is most appropriate. We found that the standard deviation for Hemoglobin A1C would be approximately 0.5% with a mean of 5.0 in normal subjects. We assume that most clinicians will consider a difference in Hemoglobin A1c of 0.3% to be clinically important. We wish to limit the Type I error rate to 0.05 or less and to achieve a power of at least 90% (i.e. a Type II error rate of 0.1). We chose the Hemoglobin A1C measurement to model this sample size estimation. Since we are planning on evaluating a total of 8 biochemical markers and survey instruments (HgA1C, lipid panel, BMI, BP, and PAM scores) we employed the Bonferroni inequality to adjust the Type I error rate. Under these assumptions, we calculate that approximately 60 participants are required. We proposed to collect an additional 6 participants in case non-parametric analysis seems appropriate.

CHR made home visits once a month to check on the participants' progress and reinforce the ideas presented in the classes. Six months after the class, the baseline lab work and clinical measurements repeated. Participants also repeated the PAM questionnaire. We hypothesize that the participants' HgA1C, lipid panel (total cholesterol, HDL, LDL, triglycerides), BMI, BP, and PAM scores will have improved from their baseline numbers taken before the education course and follow up with a CHR.

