**Secondary Outcome Measures:**

- Diabetes associated health indicators including HbA1c, Glucose, Lipids, BMI (time -6 months of education) (No safety issue)

**Enrollment:** 60 (both men and women)

Study start date: June 2012

**Study completion date:** December 2012

**Number of arms:** 1

**Eligibility:** All participants are Zuni Natives living in Zuni Pueblo, New Mexico. They are all diabetics with HbA1c level of 6.6% and above in the age range of 21 years to 75 years old.

**Sampling Method:** Non-probability samples recruited directly from the list of previous study conducted at Zuni.

**Summary Description:** The number of American Indians and Alaska Natives (AI/ANs) who have diabetes is growing rapidly, especially among young people. At more than 16%, AI/ANs have the highest age-adjusted prevalence of diabetes among all U.S. racial and ethnic groups. One such population is the Zuni Pueblo home to a small, geographically isolated tribe located in a rural portion of New Mexico, USA. It is home to ~11,000 Zuni Indians and over 90% of all Zunis live in the Pueblo. This socioeconomically disadvantaged population faces a major public health challenge from growing health disparities. Changing lifestyles have led to decreased physical activity and increased caloric intake with high consumption of fast food, soda pop and alcohol. Therefore, the Zuni are experiencing interrelated epidemics of obesity, diabetes, hypertension, kidney disease and intermediate phenotypes.

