As part of the Zuni Health Initiative (ZHI), we surveyed participants regarding barriers to healthcare, with particular attention to diabetes care. In ZHI we also collected and stored clinical phenotype information and anthropological measurements from all participants. Participants identified the following barriers: access to care, language barriers, limited patient education, and anxiety around diagnosis, fear of chronic disease, reluctance to participate in self-care, resistance to dietary change, and reluctance to engage in regular exercise. We have previously documented suboptimal glycemic control with a high burden of kidney disease among the Zuni. The burden presented by these barriers ultimately translates into a lack of patient activation and engagement in their healthcare, effectively hindering adoption of healthy behaviors. Focus groups subsequently identified common solutions to overcome some of these barriers, including home-based care, point of care testing, individualized exercise and nutrition prescriptions, and care providers with knowledge of the Zuni language, community and culture.

The information gathered during these focus groups is used to design and implement a Zuni culture specific educational intervention in diabetes. We have devised an innovative educational intervention based on the coordination of four key elements: (a) delivering healthcare that incorporated collaborative communication within the healthcare team and emphasized greater autonomy in care, adherence to the medical regimen, and patient-centered goal setting, all while retaining the ability to address the needs of patients, family members, the healthcare team, and/or the healthcare system; (b) providing innovative educational and organizational approaches, as well as behavior change strategies, that enhanced adherence; (c) addressing health beliefs that reduced adherence by over- or under-predicting maladaptive thoughts (e.g., catastrophizing, minimizing, cognitive dissonance, invincibility, or fatalism) or that interfered with weight control; and (d) using technology to address barriers to achieving desired health outcomes.

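### The HbA1c SD behind the sample size comes from normal subjects, so the 90% power claim is unsupported for this all-diabetic cohort

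*Protocol*

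**What the plan says.** The sample size paragraph in Methods is built on HbA1c alone. Its spread is described as follows: "We found that the standard deviation for Hemoglobin A1C would be approximately 0.5% with a mean of 5.0 in normal subjects". The difference of interest is 0.3%. On error rates it says "We wish to limit the Type I error rate to 0.05 or less and to achieve a power of at least 90" per cent. On sidedness it says "We anticipated that a 2-tailed statistical model is most appropriate". On multiplicity it says "Since we are planning on evaluating a total of 8 biochemical markers and survey instruments", and for that reason "we employed the Bonferroni inequality to adjust the Type I error rate". The result is about 60 participants, with 6 more proposed in case a non-parametric analysis is needed.

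The eligibility entry under Secondary Outcome Measures says of the participants: "They are all diabetics with HbA1c level of 6.6% and above". Methods requires overt diabetes, shown by fasting glucose, HbA1c or random glucose. The summary description adds: "We have previously documented suboptimal glycemic control with a high burden of kidney disease among the Zuni".

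There is one arm. Methods repeats the baseline measurements six months after the class and expects them to have improved on each person's baseline. HbA1c is listed as a secondary outcome, and the PAM score is primary.

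**The concern.** The planning SD describes a group that cannot enrol. It is also not shown to be the right kind of SD. In a one-arm before-and-after comparison, power depends on the SD of the within-person change, whereas the quoted figure, given with a mean, reads as the spread between people at one time. The protocol gives no SD for diabetics, no SD of change and no correlation between baseline and six months.

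The required number grows with the square of the SD, so a modest error in this input matters. HbA1c is the only basis given for 60 participants and for the 90% figure. If the real power is much lower, a non-significant HbA1c result would say little about whether the programme worked, yet it would be read against a stated power of 90%.

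**Working it through.** **Inputs from the protocol (Methods).** Difference d = 0.3 points; SD 0.5; two-sided; overall alpha 0.05; Bonferroni for 8 measures; power 90%; N about 60. The divisor is not written out, so I read the adjusted alpha as 0.05/8 = 0.00625.

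**Step 1: the plan's own figure.** For a paired comparison, N = (SD of change × (z for 1 − alpha/2 + z for power) / d)².
- Alpha 0.00625, SD of change 0.5: (0.5 × (2.734 + 1.282) / 0.3)² = 44.8, so 45. The exact t version gives 49.
- Alpha 0.05, SD of change 0.5: (0.5 × (1.960 + 1.282) / 0.3)² = 29.2, so 30. The exact t version gives 32.
- SD 0.5 as a cross-sectional SD with zero correlation (SD of change 0.5 × √2 = 0.707): 94 by exact t at 0.00625, and 61 at 0.05.
- Two independent groups: 92 per group by exact t at 0.00625, and 60 per group at 0.05.

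The stated 60 is therefore not recovered from a paired test at the adjusted alpha with an SD of change of 0.5. The nearest matches leave out the Bonferroni adjustment. With the adjustment, about 60 needs an unstated correlation near 0.4 (N = 58). This is a separate weakness of the same paragraph, and it means the intended formula has to be stated before any SD can be judged.

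**Step 2: what SD of change would 60 participants tolerate?** Solving the exact paired-t power (noncentral t, 59 degrees of freedom, noncentrality d√60/SD) for 90% gives:
- alpha 0.05/8: SD of change at most 0.56;
- alpha 0.05: SD of change at most 0.71 (0.705 before rounding).

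With 66 participants the limits rise only to 0.59 and 0.74.

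**Step 3: power at N = 60, d = 0.3, over a range of SDs.** The protocol gives no SD of change, so every value in the first column is an assumption.

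| Assumed SD of change | Power, alpha 0.05/8 | Power, alpha 0.05 | Change detectable with 90% power (0.05/8; 0.05) |
|---|---|---|---|
| 0.5 | 96% | 99.5% | 0.27; 0.21 |
| 0.6 | 85% | 97% | 0.32; 0.26 |
| 0.8 | 53% | 81% | 0.43; 0.34 |
| 1.0 | 31% | 63% | 0.54; 0.43 |
| 1.5 | 11% | 33% | 0.80; 0.64 |

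The detectable change is SD × 0.3/0.56 at alpha 0.05/8 and SD × 0.3/0.705 at alpha 0.05.

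**Step 4: from cross-sectional SD to SD of change.** With equal spread at both visits, SD of change = SD × √(2(1 − r)). Power at alpha 0.05/8, with SD and r both assumed:
- SD 1.0, r = 0.9: SD of change 0.45, power 99%;
- SD 1.0, r = 0.7: SD of change 0.77, power 57%;
- SD 1.5, r = 0.9: SD of change 0.67, power 73%;
- SD 1.5, r = 0.8: SD of change 0.95, power 36%.

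To stay within 0.56, r must be at least 1 − 0.56²/(2 × SD²). That is 0.84 for an SD of 1.0 and 0.93 for an SD of 1.5.

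**The case against.** The strongest reply is that a wider spread of HbA1c among diabetics does not by itself mean a wider spread of change. A high enough correlation between visits restores the power, as the first line of Step 4 shows. This stands. A reader might infer that a 0.3-point change is probably undetectable with 60 people, but the protocol does not support that, because it contains neither the SD nor the correlation needed.

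A reader might also argue from the gap between the planning mean of 5.0 and the entry threshold of 6.6%: 1.6 points, or 1.6/0.5 = 3.2 planning SDs. The gap shows that the two populations differ, but the mean does not enter the sample size formula, so the gap says nothing about the size of the shortfall. Nor is 6.6% a uniform floor. It appears in the eligibility entry, whereas Methods also accepts a diagnosis on glucose alone. All participants are diabetic under either statement, and the point needs no more than that.

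It can fairly be said, too, that HbA1c is secondary. An optimistic SD biases no estimate and does not touch the power for the PAM score. That limits the consequences. It does not excuse the input, since HbA1c is the only outcome for which a calculation is given and it alone produces the 60.

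Finally, one might assume the team already holds the right SD. The summary description says that clinical phenotype information was stored, and it reports poor glycaemic control. It does not say that repeat HbA1c values exist.

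**Conclusion.** The point holds in a limited form. The SD of 0.5% belongs to normal subjects, the participants are all diabetic, and the analysis is of within-person change. The 90% power claim is therefore unsupported for this study. The claim would be true if the SD of six-month change were no more than about 0.56 (alpha 0.05/8) or 0.71 (alpha 0.05). Beyond that, power at the adjusted alpha falls quickly, to 53% at an SD of 0.8 and 31% at 1.0. Which of these applies cannot be settled from the protocol. The figures assume 60 complete pairs, a two-sided paired t-test, and 8 as the Bonferroni divisor. Under Limitations and Biases the protocol says that attrition cannot be accounted for, and any loss of pairs would lower these powers.

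**What to change.** Keep 60 participants and rewrite the sample size paragraph:
- Replace the normal-subject SD with an SD of six-month HbA1c change in diabetics, from existing Zuni data if such data are available. Otherwise use a cross-sectional SD for diabetics with a stated range of correlations.
- State that the test is paired, give the formula, and write out the adjusted alpha with its divisor.
- Report the power for 0.3 points, and the smallest change detectable with 90% power.
- Drop the 90% claim if it does not hold.

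The cost is one rewritten paragraph, a look for suitable data, and a stated power for a secondary outcome that may well be less favourable. Enrolment and procedures do not change.

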**Evaluating a Novel Approach to Diabetes Management in**

**Zuni Indians**

**Research Protocol**

**June – Dec 2012**

## Abstract

**Purpose:** One in three people will be diagnosed with diabetes by 2050, and the proportion will likely be higher among Native Americans. Diabetes control is currently suboptimal in underserved populations such as Zuni Indians despite a plethora of new therapies. Patient empowerment is a key determinant of diabetes control, but such empowerment can be difficult to achieve due to resource limitation and cultural, language and health literacy barriers. We will conduct a home-based chronic disease (diabetes) educational intervention using Community Health Representatives (CHRs) to associate improvement in Patient Activation Measures scores (primary outcome) and clinical indicators of diabetes control (secondary outcomes).

| Condition                                                                                                                       | Intervention                                                  |
|---------------------------------------------------------------------------------------------------------------------------------|---------------------------------------------------------------|
| The study focus is on lifestyle changes and patient Activation in Diabetic Patients by regular monthly visit by the CHRs | Educational intervention of Lifestyle and patient activation. |

**Study type:** Observational

**Study Design:** Cohort, Prospective

**Biospecimens Retention:** NONE

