**Primary Outcome Measure:**

- Patient Activation (time -6 months of education) (No safety issue)  
The Patient Activation Measure (PAM) instrument completed by participants using the short form PAM questionnaire. The response options for the 13 questions use a categorical agreement scale with 4 response options: (i) strongly disagree, (ii) disagree, (iii) agree, (iv) strongly agree, and N/A. The raw score is calculated by adding responses to the 13 questions. If all questions are answered (i.e., no "N/A" is used), the range of raw scores would be 13 to 52. If there is at least 1 item with a response of N/A, the total score will be divided by the number of items completed and multiplied by 13 to yield a normalized raw score. All study procedures were repeated 6-months later, following the intervention.

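### PAM is the only primary outcome, but the trial is sized on secondary HbA1c, and PAM is counted as one of eight equal Bonferroni tests, a valid but needlessly costly split if it carries into the analysis

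*Protocol*

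**What the plan says.** The Abstract sets the hierarchy: "Patient Activation Measures scores (primary outcome) and clinical indicators of diabetes control (secondary outcomes". The Primary Outcome Measure section lists PAM and nothing else. The Secondary Outcome Measures section gives "Diabetes associated health indicators including HbA1c, Glucose, Lipids, BMI", so HbA1c is secondary.

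The sample size paragraph in Methods works from a different starting point:

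- On the endpoint: "We chose the Hemoglobin A1C measurement to model this sample size estimation". The inputs are an HbA1c difference of 0.3%, an SD of about 0.5% taken from normal subjects, a two-tailed test, a type I error of at most 0.05 and power of at least 90%.
- On multiplicity, it applies the Bonferroni inequality because the study will evaluate "8 biochemical markers and survey instruments (HgA1C, lipid panel, BMI, BP, and PAM scores".
- The result is about 60 participants, plus 6 more in case a non-parametric analysis is used.

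No PAM difference, PAM standard deviation or PAM power appears anywhere in the protocol.

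The next paragraph of Methods hypothesises improvement in HbA1c and in "lipid panel (total cholesterol, HDL, LDL, triglycerides), BMI, BP, and PAM scores". On measurement, Methods says "Baseline lab work, including a complete lipid panel, CBC, UACR, and serum creatinine collected from each participant at home prior to the class" and adds height, weight, blood pressure and HbA1c on the day of the class.

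**The concern.** A single, pre-named primary outcome normally has two consequences. The sample size is justified for it, and it can be tested at the full 0.05, because secondary outcomes need not draw on its alpha. The sample size paragraph does neither. It attaches the power statement to HbA1c and gives PAM the same standing as seven secondary measures.

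At stake is the trial's main question, whether PAM rises over six months. The reader is not told what PAM change 60 participants can detect. If the Bonferroni split governs the analysis, the primary test uses one eighth of the alpha available to it.

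A smaller matter is that the eight measures are not the declared outcomes. Blood pressure is in the family but not in the secondary list. Glucose is in the secondary list but not in the family or the hypotheses.

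**Working it through.** **Inputs.** One arm, before-after comparison (Number of arms; Methods). Two-tailed Student's t, overall alpha 0.05, power 90%, HbA1c difference 0.3, SD 0.5, eight measures, about 60 participants (Methods). The PAM effect is not given, so a range is assumed. All 60 are assumed to have both measurements.

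**1. The count of eight.** HbA1c 1 + lipids 4 (total cholesterol, HDL, LDL, triglycerides) + BMI 1 + BP 1 + PAM 1 = 8. This reproduces if BP counts once. Per-test alpha = 0.05/8 = 0.00625.

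**2. The plan's figure of 60.** For one sample of changes, n = (z for 1 − alpha/2 + z for power)² × (SD/difference)².

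- With Bonferroni and SD of change 0.5: (2.734 + 1.282)² × (0.5/0.3)² = 16.13 × 2.778 = 44.8, so 45 (49 with the t distribution).
- With Bonferroni and SD of change 0.5 × √2 (zero correlation between visits): twice that, so 90 (94 with t).
- Unadjusted alpha 0.05 and SD of change 0.5 × √2: 10.507 × 2.778 × 2 = 58.4, so 59 (61 with t). The unadjusted two-sample formula gives 59 per group (60 with t).

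The stated inputs with Bonferroni do not give 60 under these readings, while two unadjusted calculations do. With Bonferroni, 60 needs an SD of change of about 0.56, which the protocol does not state. So it is unclear whether the adjustment entered the number at all. None of these calculations involves PAM.

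**3. Detectable PAM change with n = 60.** Paired t-test, noncentral t with 59 degrees of freedom and noncentrality d × √60, where d is the mean change divided by the SD of change. Solving for 90% power:

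- alpha 0.05: d = 0.425, or 0.43 SD
- alpha 0.00625: d = 0.536, or 0.54 SD

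**4. Power for PAM over assumed effects, n = 60.**

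| Assumed change (SD of change) | alpha 0.00625 | alpha 0.05 | Loss (points) |
|---|---|---|---|
| 0.3 | 31.4% | 62.8% | about 31 |
| 0.4 | 60.5% | 86.2% | about 26 |
| 0.5 | 84.5% | 96.8% | about 12 |
| 0.6 | 96.1% | 99.5% | about 3 |

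In sample size terms (normal approximation), the split multiplies the number needed for 90% power by 16.13/10.51 = 1.53.

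**5. Error control under alternatives.**

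- PAM at 0.05 plus a separate, ungated secondary family at 0.05 bounds the overall error only at 0.05 + 0.05 = 0.10, above the protocol's limit of 0.05 if that limit covers all measures.
- PAM at 0.05, with the secondaries tested by Holm at 0.05 only after PAM succeeds, keeps the overall error at 0.05.

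**6. The lists side by side.**

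| Measure | Secondary Outcome Measures | Eight-measure family | Hypotheses | Named among baseline measurements in Methods |
|---|---|---|---|---|
| Blood pressure | no | yes | yes | yes |
| Glucose | yes | no | no | no |

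**The case against.** The strongest reply is that the Bonferroni sentence belongs to the sample size calculation. It stands directly before the resulting number, and no sentence says that PAM will be tested at 0.00625. The analysis threshold may be set in a statistical analysis plan that is not at hand. This stands in part. The adjustment is justified by the measures the study plans to evaluate, which implies the same split at analysis but does not fix it. A reader might infer that PAM is certainly tested at one eighth of alpha. The document supports that only conditionally, and step 2 leaves open whether the adjustment entered even the sample size.

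Second, Bonferroni over all eight measures is valid. It meets the stated error limit and creates no false-positive risk. This stands: the split is inefficient, not wrong.

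Third, the loss of power depends on an effect the protocol does not give, and it nearly vanishes at 0.6 SD. This also stands. A reader might infer that the trial is underpowered for PAM, but without a PAM difference or SD that cannot be shown.

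Fourth, the list mismatch is mostly editorial. The secondary list and the baseline laboratory list are both introduced with an open-ended word, so neither need be complete. A reader might go further and count ten tests by splitting blood pressure into systolic and diastolic and adding glucose. The protocol names BP as one item both times, so its own count of eight is coherent. A family of ten would also change little: alpha 0.05/10 = 0.005 gives a detectable change of 0.55 SD instead of 0.54.

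These replies do not explain why the stated power belongs to a secondary outcome, or why the primary outcome has no power statement and no clear alpha.

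**Conclusion.** The point holds in a limited form and should be fixed. On the protocol's own text, the sample size and 90% power rest on a secondary outcome, no detectable PAM change is given, and the primary outcome is counted as one of eight equal tests. If that count governs the analysis, the detectable PAM change at 90% power rises from 0.43 to 0.54 SD of change, and power falls by about 31 points at a true change of 0.3 SD but only about 3 points at 0.6 SD. These figures assume 60 complete pairs, a paired t-test and assumed PAM effects. Any error is in the conservative direction. The mismatch over blood pressure and glucose is minor.

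**What to change.** In the sample size paragraph of Methods:

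1. State that the 6-month PAM change is tested first, alone, at two-sided 0.05. Only if it is significant are the secondary outcomes tested, with Holm at 0.05. The gate is essential, because without it the overall error is bounded only at 0.10.
2. State that the 90% power refers to HbA1c, and that 60 participants with both measurements detect a PAM change of 0.43 SD of change with 90% power. This discloses what the existing number can do for PAM. It does not show that 0.43 SD matters on the PAM scale, which would need a PAM difference and SD that the protocol does not give.
3. Use one secondary list throughout. Either declare blood pressure as a secondary outcome or take it out of the tested family. Either add glucose to the family, the hypotheses and the measurement list, or delete it as an outcome.

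The cost is protocol wording and no extra participants; glucose measurement is added only if that outcome is kept. The statistical price is that a secondary outcome can be claimed only if PAM succeeds, whereas the eight-way split lets HbA1c or a lipid succeed on its own.

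### If the Bonferroni adjustment named for the eight measures is carried into the analysis, Holm's step-down procedure would give the same family-wise control and more power when several measures improve

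*Protocol*

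**What the plan says.** The sample-size paragraph of the Protocol, Methods, sets the error limits: "We wish to limit the Type I error rate to 0.05 or less", with power stated as "to achieve a power of at least 90% (i.e. a Type II error rate of 0.1". The test is to be two-sided ("We anticipated that a 2-tailed statistical model is most appropriate"). HbA1c serves as the model outcome, with a "difference in Hemoglobin A1c of 0.3% to be clinically important" and the statement that "the standard deviation for Hemoglobin A1C would be approximately 0.5% with a mean of 5.0 in normal subjects".

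The paragraph then says that "we are planning on evaluating a total of 8 biochemical markers and survey instruments", and for that reason "we employed the Bonferroni inequality to adjust the Type I error rate". A requirement of about 60 participants follows. No other multiplicity method is named in the protocol, and no rule is given for declaring each of the eight six-month results significant.

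The next paragraph of Methods, on follow-up, gives the expected pattern. It hypothesises that HbA1c and the "lipid panel (total cholesterol, HDL, LDL, triglycerides), BMI, BP, and PAM scores will have improved from their baseline numbers". Counting blood pressure once, these are the eight measures: HbA1c, four lipids, BMI, BP and PAM.

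**The concern.** Bonferroni compares every p-value with 0.00625, whatever the other seven show. When several hypotheses are false and have already been rejected, it still divides alpha by eight. The protocol's own hypothesis, improvement on all eight, is the pattern in which that division costs most.

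At stake is the chance that real six-month changes are reported as not significant when the stated error limit does not require it. Power is hard to buy here. Possible Difficulties names recruitment from a small community as a risk, and Limitations and Biases says that attrition cannot be accounted for.

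**Working it through.** **Inputs from the protocol.** Family-wise alpha 0.05, two-sided; eight measures; one arm measured before and after; about 60 participants; HbA1c difference 0.3 and SD 0.5.

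**Inputs assumed.** The protocol gives no SD of change, no correlation between measures, and no effect for any measure except HbA1c. Effects below are in SDs of change.

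**The plan's own figure.** The per-measure alpha is 0.05/8 = 0.00625. For a paired comparison with 0.5 taken as the SD of change:

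n = [SD × (z(1 − alpha/2) + z(power)) / difference]² = [0.5 × (2.734 + 1.282) / 0.3]² = 44.8, so 45, or 49 with the t distribution.

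If 0.5 is the SD at each visit and the visits are uncorrelated, the SD of change is 0.5 × √2 = 0.707, and n is 90 (normal) or 94 (t). The stated 60 is therefore not reproduced. It would need an SD of change of about 0.56, which is not stated. That is a separate matter; n = 60 is taken as given below.

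**Error control under Holm.** Order the p-values and compare them in turn with 0.05/8, 0.05/7, and so on up to 0.05, stopping at the first failure.

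- If m0 hypotheses are true, the first true one to be rejected can meet a threshold no larger than 0.05/m0. The chance that any of the m0 falls below that is at most m0 × 0.05/m0 = 0.05, whatever the correlation.
- Any p-value at or below 0.05/8 passes every Holm threshold it meets, so Holm keeps every Bonferroni rejection.
- The first Holm threshold equals Bonferroni's, so the chance of at least one rejection is the same.

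**Power at n = 60.** Simulated paired t-tests on eight measures; repeat runs move the figures by about a point. Correlation between measures is 0 to 0.3, except in the 0.424 row, where it is 0 to 0.6.

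| True pattern | Average power per improving measure: Bonferroni | Holm |
|---|---|---|
| All eight, 0.3 SD | 32% | 37-39% |
| All eight, 0.4 SD | 61% | 74-75% |
| All eight, 0.424 SD (0.3/0.707) | 67% | 78-82% |
| All eight, 0.5 SD | 84-85% | 94-96% |
| All eight, 0.6 SD (0.3/0.5) | 96% | 99% |
| Four of eight, 0.4 SD | 61% | 64-65% |
| One of eight, 0.6 SD | 96% | 96% |

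Power to show all eight, which is the hypothesis as written, rises from 2-11% to 25-41% at 0.4 SD and from 73-77% to 96% at 0.6 SD. If HbA1c moves by 0.6 SD and the other seven by 0.2 SD, power for HbA1c is 96% under both methods. Family-wise error under Holm was at most 0.05 in every setting.

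**The case against.** The strongest objection concerns what the text fixes. The Bonferroni sentence stands between the choice of HbA1c as the planning outcome and the resulting sample size. Read in place, it sets a planning alpha. A reader might infer that the protocol commits the analysis to single-step Bonferroni, but it does not say so, and an SAP that is not shown may set the decision rule. Planning at 0.05/8 is also compatible with a Holm analysis, because Holm's first threshold is the same. All of this stands, and it makes the point conditional. The point is not empty, because the reason given for adjusting is that eight measures will be evaluated. That reason applies to the analysis, and no other method is named.

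The second objection is size. At 0.6 SD, the only ratio that can be formed from the protocol's figures, the gain per measure is about 3 points. Larger gains need smaller effects shared by all eight measures, and a hypothesis that all improve is not evidence that they do. This also stands. The gain depends on how many measures truly change, and it can be nil but not negative.

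The third is that PAM is the primary outcome and the clinical indicators are secondary, so a flat Holm procedure would let PAM's threshold depend on secondary results. That threshold would never be stricter than 0.05/8, so PAM is no worse off than under Bonferroni. Which measures belong in one family is a separate question that this point does not settle.

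**Conclusion.** The point holds as a conditional efficiency improvement. If the named adjustment governs the analysis, Holm gives the same family-wise guarantee and loses no rejection. Under the protocol's hypothesis that all eight measures improve, it adds about 13 to 14 points of average power per measure at 0.4 SD (61% to 74-75%) and about 3 points at 0.6 SD. The last figure takes 0.5 as the SD of change and applies the resulting 0.6 SD to all eight measures. With four improving by 0.4 SD the gain is about 4 points.

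Two stronger readings are not supported. A reader might infer that Type I error is badly controlled, but Bonferroni meets the stated limit. A reader might also infer that fewer participants are needed. If HbA1c must have 90% power whatever the other measures show, the requirement stays at 49 (paired t, SD of change 0.5), as under Bonferroni. It falls to 32 only if the other seven have already been rejected.

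The effect sizes, the SD of change and the correlations are assumptions. Testing systolic and diastolic pressure separately would make the family nine and would not change the conclusion.

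**What to change.** State in the protocol or SAP that the measures tested together will be analysed with Holm's step-down procedure at a family-wise two-sided 0.05. Report Holm-adjusted p-values beside confidence intervals that are labelled as unadjusted. Keep 0.05/8 as the planning alpha and say that it serves that purpose.

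The cost is a sentence or two. The one drawback is that Holm has no simple matching simultaneous confidence intervals, whereas Bonferroni does. An unadjusted interval may therefore exclude zero while the adjusted p-value exceeds 0.05, and the text should say which of the two decides significance.
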